### Blinding

Patients, research psychiatrists, radiologists, statisticians, and neuropsychologists who measure the primary and second outcomes will be blinded to the randomization status from beginning to end. Participants will not distinguish the group they belong to, will not have precise description of iTBS and training parameters, and will not be allowed to speak to each other. Meanwhile, blinding will be maintained for outcome assessment, data management, and analysis.

### Follow-up

Investigators will meet participants on the baseline, ending of trials, and 3 and 6 months after the last treated session. A concerned call is needed to keep in contact with patients and remind them of the next interview in order to avoid being lost to follow-up.

### Intervention

#### The iTBS+WMT group: the study group

During each treatment, the patient received 3 min and 20 s of iTBS stimulation, followed by a 1–2-min short-time rest and 40 min of working memory training immediately (Fig. 1).

**Fig. 1 Fig1:**

The iTBS+WMT group

iTBS (provided by YiRuiDe CCY-II therapeutic instrument, Wuhan, China) used standard international-approved parameters (120% RMT stimulation intensity or 40% intensity; triplet 50 Hz bursts, repeated at 5 Hz; 2 s on and 8 s off; repeat 20 times; 600 pulses per session; total duration of 3 min 20 s) [25, 29, 30]. After professional testing, the magnetic field intensity has reached the effective range. The left dorsolateral prefrontal cortex is located in each patient with a positioning hat, which was previously proved as optimal target on the basis of clinical finding and whole brain MRI [31]. Initial treatment comprised 30 sessions in total, which consisted of once-daily sessions (on weekdays; i.e., five sessions a week).

The WMT training tool belongs to a computer training system based on the working memory theory model and cognitive processing process that is self-developed and validated by pre-clinical studies. This set of training shows the most typical working memory paradigm, that is, the subjects try to memorize a series of continuous materials (including numbers, languages, pictures) of random length (length is not fixed), and judge the sequence of the last 2–4 materials after presentation. The total number of working memory training sessions is 30, 40 min each, five times a week for 6 weeks.

#### The iTBS+SRT group: the WMT control group

The iTBS stimulation method is the same as that of the study group. It is not to practice WMT after the end of the stimulation, but instead to use simple response training (Fig. 2). For example, when a specific shape (such as a red triangle) exists in many sequentially presented geometries, the patient needs to press a key (space). In order to avoid the influence of the material on the result, the material of SRT is exactly the same as that used in WMT training, and this process has no working memory processing content, so it can be used as a comparison condition of WMT.

**Fig. 2 Fig2:**

The iTBS+SRT group

#### The sham iTBS+WMT group: the iTBS control group

During each treatment, the patient performs about 3 min and 20 s of sham iTBS. On sham stimulation, a plastic model with the same shape as the coil is fixed on the real coil. This coil has a magnetic shield that reduces the diffusion of the magnetic field under its surface. The distance between the model and the real coil is about 6 cm, which makes the magnetic field generated by the coil basically disappear on the scalp surface. The magnetic field intensity is almost 0 Tesla. So it cannot induce any significant physiological transcranial effect on the brain. After stimulation, the participants perform working memory training at a short interval (1–2 min), and the training method and duration are exactly the same as those of the study group (Fig. 3).

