### Participants

Two hundred patients with schizophrenia will be recruited on fulfillment of the inclusion criteria. The patients will be randomly allocated into four groups, i.e., the study group (iTBS+WMT), WMS control group (iTBS+ Simple Response Training, SRT), iTBS control group (sham iTBS+WMT), and placebo control (sham iTBS+SRT). Patients will be recruited in two specialty neurostimulation centers at Beijing Huilongguan Hospital, Shenyang Anning Hospital.

This trial has been approved by the local Ethics Committee and followed close to the principles of the Declaration of Helsinki (version 2004). And Standard Protocol Items: Recommendations For Interventional Trials (SPIRIT) Checklist is detailed in additional file according to requirements. All of the patients sign a written consent form in order to take part in the study, after acquainting the aim and procedures.

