### Neuropsychological assessment

Cognitive function: MATRICS Consensus Cognitive Battery (MCCB) and Wechsler Adult Intelligence Test Brief Version (WAIS-R) as special measures for evaluating cognitive function in schizophrenia.
1.1Evaluation indicators of primary training effect (working memory): spatial span, digital sequence, verbal memory (Hopkins Verbal Learning and Memory Test (HVLT)), visual memory (Brief Visuospatial Memory Test (BVMT)).1.2Evaluation index of migration effect:
1.2.1Psychomotor speed: symbol code; trial making A; category fluency1.2.2Reasoning and problem solving: maze test1.2.3Social cognition: emotion management, verbal emotion recognition test (VERT), face emotion recognition test (FERT)1.2.4Attention: continuous performance test (CPT)Clinical symptoms: the Chinese version of the Positive and Negative Symptoms Scale (PANSS), the Concise Negative Symptoms Scale (BNSS), and the Clinical Global Impression (CGI) were used to evaluate clinical symptoms through the semi-fixed inspection method. These were assessed by four clinical training senior physicians in each center.Social function: Personal and Social Performance Scale (PSP)Others: Quality of Life Scale (SQOLS), Temporary Pleasure Experience Scale (TEPS), Self-esteem Scale (SES), the visual analogue scale (VAS) of side effects

All the above scales were evaluated blindly by the raters, who were unaware of the treatment methods used by the patients. Except for the WAIS-R, which was evaluated only once at the baseline, the other scales were assessed at four time points (before and after the training and 3 and 6 months of follow-up).

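### The sham has almost no field at the scalp and no described sensory substitute, so the flat blinding claim is unsupported; the side-effect scale also goes through the blinded raters

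*Protocol article*

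**What the plan says.** - **Sham (Intervention, sham iTBS+WMT group).** For sham stimulation, "a plastic model with the same shape as the coil is fixed on the real coil". The gap is about 6 cm, "which makes the magnetic field generated by the coil basically disappear on the scalp surface". The section adds: "The magnetic field intensity is almost 0 Tesla". The sham iTBS+SRT arm uses the same sham.
- **Active (Intervention, text under Fig. 1).** Intensity is given as "120% RMT stimulation intensity or 40% intensity", with 600 pulses per session. "Initial treatment comprised 30 sessions in total", once daily on weekdays.
- **Patient blind (Blinding).** "Participants will not distinguish the group they belong to". The supports named are that patients receive no precise description of the iTBS and training parameters and may not speak to each other.
- **Rater blind (Neuropsychological assessment).** The list of scales ends with the VAS of side effects. It is followed by: "All the above scales were evaluated blindly by the raters, who were unaware of the treatment methods used by the patients".
- **Expected events (Data monitoring).** Mild headache and irritability are anticipated from the intervention. They are to be eased by rest or by spacing the stimulation.

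**The concern.** The primary objective is facilitation of working memory training by iTBS, so it rests on active versus sham stimulation, chiefly iTBS+WMT versus sham iTBS+WMT. If patients can tell which stimulation they receive, expectation and effort differ between exactly these arms. If raters can tell, judgement-based scores (PANSS, BNSS, CGI, PSP) can differ too. Neither randomisation nor the repeated-measures analysis of variance removes such a difference, because it arises after allocation and follows the treatment. The report would still call the trial double-blinded. The article presents patient blinding as a certainty, yet its own description of the sham gives a reason to doubt it. It also sends a measure that may hint at the arm to the people it needs to keep blind.

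**Working it through.** The protocol gives no figure on blinding to reproduce, so the check sets its statements side by side.

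**1. What each arm receives.** Active: 600 pulses × 30 sessions = 18,000 pulses at the stated intensity. Sham: the same number of sessions with a field near zero at the scalp, which the article says cannot produce a significant physiological effect on the brain. Any local sensation that depends on the field reaching the scalp is therefore missing from the sham. No substitute for it is described in either sham arm.

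**2. What the safeguards cover.** Withholding parameters limits what a patient has been told. Forbidding conversation limits comparison between patients. The model has the same shape as the coil and is mounted on the real coil, so appearance, and possibly noise, are preserved. None of these concerns sensation under the coil, repeated over 30 sessions. The unqualified statement in Blinding therefore does not follow from the measures described.

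**3. The rater route.**
- The sentence on blind evaluation covers all the scales above it, and the side-effect VAS is one of them.
- Data monitoring expects headache and irritability. One of the two remedies it names is spacing the stimulation, which suggests that stimulation is thought to be at least part of the cause.
- The scales are taken at baseline, post-treatment, and 3 and 6 months. Baseline precedes stimulation and the last two come months after it, so exposure is mainly at the post-treatment visit.
- The route is avoidable: nothing in the article requires the efficacy raters to see this scale.

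**4. Size.** If believing oneself on active stimulation is worth *e* SD, the spurious difference is

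bias = *e* × (share of active patients believing active − share of sham patients believing active).

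The documents give none of these three quantities. As a pure illustration with an assumed *e* = 0.2:
- shares of 70% and 40% give 0.2 × 0.30 = 0.06 SD;
- shares of 90% and 10% give 0.2 × 0.80 = 0.16 SD;
- equal shares give 0.

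The result depends entirely on the assumed inputs. It shows the mechanism and is not an estimate for this trial.

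**5. What a guess question would deliver.** For a two-way guess, the arm-level index is 2*p* − 1, where *p* is the share guessing correctly. Its 95% half-width at *p* = 0.5 is 1.96 × 2 × √(0.25/*n*). With 1:1:1:1 allocation of 200 patients, 100 receive each type of stimulation, and the half-width is 0.196. After the 20% dropout allowed for under Sample size, *n* = 80 and it is 0.219. That is precise enough to show a seriously broken blind.

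**The case against.** The strongest reply is that much of the worry rests on silence in a condensed article, and that the plan has real safeguards. Several points stand.

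- **No check of the blind.** A reader might infer that blinding is never tested. The article describes no check, but guess forms and baseline history items commonly sit in the full protocol or case report form, which are not shown. Their absence is not itself a fault.
- **Patients with earlier TMS.** Because "Patients will be recruited in two specialty neurostimulation centers" and the eligibility lists do not mention earlier TMS, a reader might infer that experienced patients will be enrolled and will recognise the sham. The phrase describes the sites. Nothing says that such patients will enter, or how many.
- **Motor threshold.** A reader might infer that sham patients feel real pulses during threshold measurement. Intensity is given as two alternatives, and the article does not say that sham patients have a threshold measured.
- **Raters.** A reader might infer that a reported headache reveals the arm to the person scoring MCCB or PANSS. The article does not say that one person handles both, or who fills in the VAS. It does not attribute headache to stimulation alone, and every arm also has 40 minutes of training per session.
- **Magnitude.** Dividing the illustrative 0.06 and 0.16 SD by the 0.29 in the Background gives 21% and 55%, and a reader might take that as the share of the effect at risk. The inputs are assumed, and 0.29 is the effect of cognitive training on working memory, a different contrast from iTBS versus sham.
- **Nature of the outcome and design.** MCCB is a performance battery, which limits expectancy effects without excluding them. The SRT arms use the same sham, so an additive belief effect would cancel in a difference of differences. However, Statistical analysis describes comparisons between two groups and does not commit to that contrast.

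These replies narrow the point. They do not reconcile the sham as specified with the unqualified patient-blinding claim, or explain why the side-effect scale is listed with the blind-rated outcomes.

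**Conclusion.** The point holds in limited form. The sham described cannot reproduce sensation that depends on a field at the scalp, so the certainty expressed in Blinding is unsupported. That patients will notice the difference is an inference from the sham's specification; the documents give no unblinding rate. Placing the side-effect VAS with the blind-rated scales opens an avoidable route to rater unblinding, mainly at the post-treatment visit. The documents do not show that the blind will fail, and the size of any bias cannot be derived from them. This is a cheap improvement that protects and tests the trial's central contrast; it does not invalidate the design.

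**What to change.** 1. Have the side-effect VAS completed by the patient, or collected by staff who score no outcomes, such as the stimulation operator. Withhold it from the MCCB, PANSS, BNSS, CGI and PSP raters. Self-completion is preferable where feasible, since an operator who knows the arm could colour the answers.
2. Ask patients to guess the stimulation arm after the first week and again at the end of treatment, and ask raters at the end of treatment. Report a blinding index by arm as a description. Do not present the iTBS effect by guess as an adjusted estimate: the guess is made after randomisation and may reflect benefit.
3. Record prior TMS exposure at baseline for a descriptive sensitivity analysis. Leave eligibility unchanged, because recruitment is already under way.
4. Reword Blinding to say that blinding of participants is attempted by the measures listed and will be assessed.

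Cost: one baseline item, one or two short questions, and a change in who handles one form. Late guesses may partly reflect perceived benefit, which is why patients are also asked early. For patients already enrolled, the early guess may no longer be obtainable, and the report should say so.

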**Fig. 3 Fig3:**

Sham iTBS+WMT group

#### The sham iTBS+SRT group: the placebo control

During each treatment, the iTBS stimulation method is the same as that of the iTBS control group. After stimulation, the participants perform simple response training at a short interval (1–2 min), which is exactly the same as those of the WMT control group (Fig. 4).

**Fig. 4 Fig4:**

The sham iTBS+SRT group

Implementing intervention will not require alteration to usual care pathways (minimize changes in dose of medications).

### Primary outcome measures

The primary outcome measures are cognitive function measured by the MATRICS Consensus Cognitive Battery (MCCB).

### Secondary outcome measures

The secondary outcomes are changes in neuroplasticity, as measured by MRI including plasticity and functional plasticity of brain structures and other behavioral assessments. Structural plasticity refers to the analysis of brain gray matter and white matter structure, while functional plasticity includes task-related brain function activation magnitude and task-related functions. Other behavioral assessments include Positive And Negative Syndrome Scale (PANSS), Brief Negative Symptom Scale (BNSS), Personal and Social Performance Scale (PSP), Temporal Experience of Pleasure Scale (TEPS), Self-Esteem Scale (SES), and the visual analogue scale (VAS) of side effects.

### Data collection

At baseline, the following data will be collected: demographic data (age, gender, education, and occupation and so on), smoking, the current medication, concomitant medications, results from a detailed physical examination and neurological examination, and neuropsychological assessment; inclusion and exclusion criteria will be evaluated with electronic case report form (eCRF) by [name]. The brain functional and structural MRI will be performed, which just conducted in Beijing Huilongguan Hospital. Because there is no MRI equipment, patients in Shenyang Anning Hospital will not do MRI scanning. In order to compare the difference of brain function between patients and normal people, 50 normal subjects matched with patients of age, sex, and education were selected before treatment for the same MRI imaging in Beijing Huilongguan Hospital.

A follow-up assessment will be scheduled at three time points: post-treatment (after 6 weeks of cognitive training) and 3 months and 6 months after end-treatment point. Data from the following examinations will be collected: neuropsychological assessment and functional and structural brain MRI (just for patients in Beijing Huilongguan Hospital) (Fig. 5). During the whole trial period, we will give participants some subsidies to increase their enthusiasm for participating in the study to promote successful completion and follow-up.

**Fig. 5 Fig5:**
[figure not shown]
Overview of the flow of participants through the trial

### Neuropsychological assessment

Cognitive function: MATRICS Consensus Cognitive Battery (MCCB) and Wechsler Adult Intelligence Test Brief Version (WAIS-R) as special measures for evaluating cognitive function in schizophrenia.
1.1Evaluation indicators of primary training effect (working memory): spatial span, digital sequence, verbal memory (Hopkins Verbal Learning and Memory Test (HVLT)), visual memory (Brief Visuospatial Memory Test (BVMT)).1.2Evaluation index of migration effect:
1.2.1Psychomotor speed: symbol code; trial making A; category fluency1.2.2Reasoning and problem solving: maze test1.2.3Social cognition: emotion management, verbal emotion recognition test (VERT), face emotion recognition test (FERT)1.2.4Attention: continuous performance test (CPT)Clinical symptoms: the Chinese version of the Positive and Negative Symptoms Scale (PANSS), the Concise Negative Symptoms Scale (BNSS), and the Clinical Global Impression (CGI) were used to evaluate clinical symptoms through the semi-fixed inspection method. These were assessed by four clinical training senior physicians in each center.Social function: Personal and Social Performance Scale (PSP)Others: Quality of Life Scale (SQOLS), Temporary Pleasure Experience Scale (TEPS), Self-esteem Scale (SES), the visual analogue scale (VAS) of side effects

All the above scales were evaluated blindly by the raters, who were unaware of the treatment methods used by the patients. Except for the WAIS-R, which was evaluated only once at the baseline, the other scales were assessed at four time points (before and after the training and 3 and 6 months of follow-up).

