### Data monitoring

The project management group is composed of [name] and [name]. The group is mainly responsible for managing the overall work of the two centers and reviewing every 6 weeks. The trial auditing group is composed of two staff members of the audit department and is responsible for regularly reviewing the progress, authenticity, and safety every 6 weeks. [name] is independently responsible for all data monitoring of the study. The intervention may produce mild adverse events, such as headache and irritability, which can be improved by giving the patient rest or interval stimulation. If the patients show unbearable, they can opt out of the trial. We should report this situation to the supervisory department for record. The trial auditing group and the independent Data Monitoring and Ethics Committee have to review conduct throughout the trial period.

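### As scheduled, the side-effect VAS has no rating within the 6-week, 30-session stimulation course, so it may under-record effects that arise during treatment

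*Protocol article*

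**What the plan says.** All references are to the protocol article.

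- **Outcome.** Secondary outcome measures includes "the visual analogue scale (VAS) of side effects" among the other behavioural assessments. No other side-effect instrument is named.
- **Timing.** Neuropsychological assessment lists the scale again under its last item ("Self-esteem Scale (SES), the visual analogue scale (VAS) of side effects") and then sets one rule for the whole list: "Except for the WAIS-R, which was evaluated only once at the baseline, the other scales were assessed at four time points". It gives these as before training, after training, and at 3 and 6 months. Only the WAIS-R is exempt.
- **Visits.** Follow-up agrees: "Investigators will meet participants on the baseline, ending of trials, and 3 and 6 months after the last treated session". So does Data collection: "A follow-up assessment will be scheduled at three time points: post-treatment (after 6 weeks of cognitive training", followed by visits at 3 and 6 months.
- **Exposure.** The description of the study-group intervention says: "Initial treatment comprised 30 sessions in total, which consisted of once-daily sessions (on weekdays; i.e., five sessions a week". The training given after each stimulation runs on the same pattern for 6 weeks.
- **Expected effects.** Data monitoring says: "The intervention may produce mild adverse events, such as headache and irritability". It adds that rest or spacing of the stimulation can improve them, that a patient who cannot bear them may leave the trial, and that this is reported to the supervisory department. An auditing group reviews safety, among other things, every 6 weeks.

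**The concern.** The four-visit schedule suits cognition, symptoms and social function, where the question is change from baseline and how long it lasts. A side-effect scale asks something else: what happens while the patient is being stimulated. Applying the same four visits to it leaves the whole exposure period without a rating.

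Two kinds of patient are affected. One has headache or irritability during the course that has settled by the time of the post-treatment visit. The other finds the effects unbearable and leaves, and may never reach that visit. If real iTBS produces more of either than sham, a comparison based on the stated ratings could make the two look more alike than they were. This matters because the abstract's discussion says that, given a significant and lasting benefit, the combination could be considered as a first-line protocol. Tolerability would be part of that judgement.

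**Working it through.** No power or sample-size formula is involved. The check is a count of ratings against sessions.

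**Inputs**
- Sessions per week: 5 (study-group intervention).
- Length of course: 6 weeks (same section, and the post-treatment visit in Data collection).
- Stated number of sessions: 30 (same section).
- Ratings on the side-effect scale: 4, at the times given under Neuropsychological assessment.

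**Step 1: reproduce the stated number of sessions.** Sessions = sessions per week × weeks = 5 × 6 = 30, which matches.

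**Step 2: place each rating against the course.**

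| Rating | Position relative to the 30 sessions |
|---|---|
| Before training | before session 1 |
| After training | after session 30 |
| 3 months | about 3 months after session 30 |
| 6 months | about 6 months after session 30 |

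**Step 3: count.** Ratings between session 1 and session 30: 0 of 4. All 30 sessions fall between the first and second ratings, about 6 weeks apart. Of the three ratings after baseline, only the post-treatment one is close to the exposure.

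**Step 4: rule out another reading of the timing.** The words on rating before and after training cannot mean before and after each session, because the rule gives the total as four. Follow-up and Data collection list the same visits and add none within the course.

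**Step 5: compare with the effects the article expects.** Data monitoring describes effects that arise from the intervention and have two outcomes: improvement with rest or spacing, or the patient opting out. A rating made only after session 30 is badly placed for the first and may not be obtained for the second.

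**The case against.** Four points on the other side deserve weight.

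1. **Adverse events are handled during the course.** A reader might infer from the schedule that side effects during stimulation go unrecorded. The article does not support that. Responding with rest or spacing implies that staff notice events at sessions, opt-outs for intolerance are reported, and safety is reviewed every 6 weeks. Routine adverse-event logging may well be in the full protocol or the eCRF, and the participant-flow figure is not available here. This stands, and it confines the point to the timing of the named scale.

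2. **No recall period is given.** If the post-treatment rating asks about the past 6 weeks, it does cover the course. This also stands in part. Such a rating would still be retrospective, could not tie an effect to a session, and might not be obtained from early leavers. Nor does the article call the effects transient; it calls them mild and improvable by rest.

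3. **The loss of early stoppers cannot be sized.** A reader might apply the 20% dropout allowance in Sample size to all 200 patients and treat the result as patients without a rating after stimulation starts. The article does not support this. The 20% is an overall maximum used to inflate the group size and is not tied to the 6-week course. A patient lost after the post-treatment visit would already have that rating. The analysis is by intention to treat, and nothing says that early stoppers are not assessed.

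4. **Neither bias nor a blind safety review is shown.** The article specifies no real-versus-sham safety test, so a reader should not conclude that such a comparison is certain to be biased. Nor does it follow that the auditing group has no systematic on-treatment data: logging may exist outside the article. Enrolment is also staggered, so each review can include patients who have already completed the post-treatment rating.

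What the objections leave untouched is that the article states this schedule outright for a named secondary outcome, and it fits that outcome badly.

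**Conclusion.** The point holds as one about the stated timing of the scale: 0 of 4 ratings fall within the 30-session course, and one post-course rating carries nearly all the information on side effects of stimulation. It may miss or under-record effects that settle within the 6 weeks, and it may not reach patients who stop early. Both could understate a real-versus-sham difference. The size of any understatement cannot be calculated, because the article gives no side-effect rates, no recall period and no dropout figure for the treatment phase.

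This rests on two assumptions: that the four-time-point rule applies to the side-effect scale as written, and that some effects fade before the post-treatment visit or lead patients to stop before it. It is a weakness in the measurement of a secondary outcome. The cognitive primary outcome is not affected. The change is worth making because it is cheap.

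**What to change.** Keep the four existing time points. Add the same scale during the treatment course, for example once a week after a session, and at the last attended session for anyone who stops. State the recall period (for example, since the last rating). Summarise by real versus sham iTBS, for instance as the proportion of patients with any new side effect and the maximum severity during the course.

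Cost: at one rating a week for 6 weeks, about six short self-ratings per patient, made at sessions they already attend five times a week, plus one eCRF page. The downside is that small added burden. If the full protocol or the eCRF already collects side effects at sessions, a sentence in the article saying so, and saying how those records will be compared between real and sham iTBS, would largely answer the point.
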